## Abstract

**Background:**

It is difficult to achieve a balance among safety, efficacy, and cost for the clinical treatment of plaque psoriasis. The current treatment of psoriasis often involves comprehensive therapy such as topical plasters, internal medicine, and phototherapy, which are expensive, and some of the drugs have serious side effects. Moving cupping is a type of cupping that has been used clinically for thousands of years in China. It has the advantage of being inexpensive and easy to perform. Therefore, it is widely used in public hospitals in China for psoriasis treatment. However, a comprehensive evaluation of the current clinical evidence of its efficacy is lacking. In this study, we aimed to evaluate the efficacy and safety of moving cupping to treat plaque psoriasis.

**Methods:**

A multicenter, two-arm parallel group, single-blind, randomized, controlled trial will be conducted at six hospitals in China between August 1, 2019 and December 31, 2021. A total of 122 adult patients (aged 18–65 years) who meet the inclusion criteria are being recruited. Participants will receive either basic treatment combined with moving cupping therapy or basic treatment combined with moving cupping placebo. The treatment cycle will be 4 weeks, and the efficacy of treatment will be assessed weekly by the Psoriasis Area and Severity Index during the treatment period and follow-up visits at weeks 6 and 8. The body surface area, physician’s global assessment, Dermatology Life Quality Index, patient-reported quality of life, visual analog scale, Traditional Chinese Medication syndrome scoring scale, combined medication, and adverse events will also be recorded and compared to the relative baseline values.

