### Objectives and hypotheses

Moving cupping is widely used as a CAM therapy. The aim of this RCT is to evaluate the efficacy of moving cupping as a plaque psoriasis treatment. The hypothesis of this study is that the Psoriasis Area and Severity Index (PASI), used as the primary endpoint to demonstrate the clinical efficacy of plaque psoriasis treatment, will be decreased significantly with moving cupping treatment compared to placebo treatment [27]. Secondary endpoints, including body surface area (BSA), Physician’s Global Assessment (PGA), Traditional Chinese Medicine syndrome scoring scale (TCMSSS), and patient-reported outcomes (Dermatology Life Quality Index [DLQI] and visual analogy scale [VAS]), for the evaluation of post-treatment clinical efficacy, psychology, quality of life, and degree of pruritus will also be considered. This study complies with the relevant Standard Protocol Items: Recommendations for Interventional Trials (SPIRIT) Checklist (Supplementary file 1) [28].

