## Methods

### Study design

The proposed study is designed as a prospective, multicenter, two-arm parallel group, single-blind RCT. Patients with plaque psoriasis will be randomly assigned to the treatment group (moving cupping) or the placebo group (sham moving cupping). Eligible participants will receive 4 weeks of treatment and a total of 8 weeks of follow-up (Table 1).

**Table 1 Tab1:** Study schedules of enrollment, intervention, and assessment

	Study period							
	Enrollment	Allocation	Treatment period				Follow-up period	
Time point	-week_1_	0	week_1_	week_2_	week_3_	week_4_	week_6_	week_8_
Enrollment								
Eligibility screen	**×**							
Informed consent	**×**							
List other procedures	**×**							
Allocation		**×**						
Interventions:								
Basic treatment plus moving cupping therapy								
Basic treatment plus moving cupping placebo								
Assessments:								
PASI	**×**	**×**	**×**	**×**	**×**	**×**	**×**	**×**
BSA	**×**	**×**	**×**	**×**	**×**	**×**	**×**	**×**
PGA	**×**	**×**	**×**	**×**	**×**	**×**	**×**	**×**
DLQI		**×**	**×**	**×**	**×**	**×**		
VAS		**×**	**×**	**×**	**×**	**×**	**×**	**×**
TCMSSS		**×**	**×**	**×**	**×**	**×**		
Vital signs	**×**	**×**	**×**	**×**	**×**	**×**		
Routine blood test	**×**					**×**		
Blood biochemical test	**×**					**×**		
Routine urine test	**×**					**×**		
Food allergen test	**×**							
Combined medications	**×**	**×**	**×**	**×**	**×**	**×**		
Pregnancy test	**×**							
Physical examination	**×**					**×**		
Adverse event		**×**	**×**	**×**	**×**	**×**		
Serious adverse events		**×**	**×**	**×**	**×**	**×**		

BSA, body surface area; DLQI, Dermatology Life Quality Index; PASI, Psoriasis Area and Severity Index; PGA, Physician’s Global Assessment; PR-QoL, patient-reported quality of life; TCMSSS, Traditional Chinese Medicine syndrome scoring scale; VAS, visual analog scale

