### Primary parameters

PASI: Incorporates the extent of psoriasis at four anatomical sites by evaluating signs of erythema, scale, and elevation. PASI scores range from 0 to 72. The primary outcome of the RCT is the proportion of patients with a reduction in PASI scores of ≥ 75% compared to baseline at the 4‑week follow-up visit [27].

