### Statistical analysis

In this study, quantitative variables (PASI, DLQI, R-QoL, VAS) with normal distributions will be described as means and standard deviation; non-normal distribution will be summarized as median and interquartile range. Quantitative variables will be compared using a Student *t* test for normally distributed variables and the Wilcoxon rank-sum test for non-normally-distributed variables. Qualitative variables (sex, age) will be summarized as frequency and proportions, and the chi-square or Fisher exact test will be used to test the differences between qualitative variables. Quantitative variables with repeated measures will be applied with general linear models. *P* < 0.05 will be considered statistically significant. All statistical analyses will be performed with SAS version 9.4 statistical package (SAS Institute Inc., Cary, NC, USA). The measurer will be blinded to the results.

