This study will be the first placebo-controlled study of moving cupping for the treatment of plaque psoriasis with multiple centers, double-arm parallel groups, and a single-blind RCT. Furthermore, the study has several advantages. The first is that it will use a placebo control to exclude the placebo effect, reduce the risk of bias, and define the clinical efficacy of moving cupping for the treatment of plaque psoriasis. The second advantage is that, because of the large land area of China, the study will include a total of six hospitals in different regions, thus including various ethnic and socioeconomic populations. As such, its experimental design will increase the generalizability of the trial outcomes. However, this study also has some limitations. Due to the particularity of moving cupping therapy, it is difficult for different operators to maintain the same strength when moving the cup. Furthermore, because different cup sizes will be selected for the different treatment sites, adsorption forces will be inconsistent. All of these limitations may lead to the risk of bias. The placebo cupping therapy method has been used previously in only two clinical trials [37, 38]. Although the moving cupping placebo lacks absorption during treatment, we found that most patients do not understand the specific operation of the treatment method; therefore, they cannot distinguish between the moving cupping placebo and moving cupping. Patients were blinded to whether they are accepting real or placebo cupping. In conclusion, this study aims to verify whether moving cupping therapy is effective for treating plaque psoriasis. We also hope to provide a safe and effective treatment for plaque psoriasis through this study.

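### The abstract names baseline as the only comparator for the secondary outcomes and adverse events, and the Statistical analysis section never states that these are compared between cupping and sham

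*Protocol article*

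**What the plan says.** In the abstract (Methods), one sentence covers the weekly PASI assessments. The next lists body surface area, PGA, DLQI, patient-reported quality of life, VAS, the TCM syndrome score, concomitant medication and adverse events, and ends: "combined medication, and adverse events will also be recorded and compared to the relative baseline values". It names no comparison with the sham arm.

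Elsewhere the article points to a between-arm question:

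- Study design: "The proposed study is designed as a prospective, multicenter, two-arm parallel group, single-blind RCT".
- Objectives and hypotheses: PASI "will be decreased significantly with moving cupping treatment compared to placebo treatment". The secondary endpoints follow in the same paragraph, without a stated comparator.
- Discussion: an advantage claimed for the trial is that "it will use a placebo control to exclude the placebo effect, reduce the risk of bias, and define the clinical efficacy".

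The Statistical analysis section says that "quantitative variables (PASI, DLQI, R-QoL, VAS) with normal distributions will be described as means and standard deviation", and that such variables are compared by a "Student *t* test for normally distributed variables and the Wilcoxon rank-sum test for non-normally-distributed variables". For categorical data: "Qualitative variables (sex, age) will be summarized as frequency and proportions, and the chi-square or Fisher exact test will be used". Repeated quantitative measures go into general linear models whose factors and contrast are not given. The section does not say that any of these comparisons is between arms, and it does not mention body surface area, PGA, the TCM score, concomitant medication or adverse events.

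**The concern.** A comparison with baseline has the null hypothesis of no change over time. Patients in both arms receive mandatory moisturiser, bathing and lifestyle advice (Basic treatment), and the sham follows the same manipulation as real cupping, in which Vaseline is applied first. Expectation and regression to the mean also act in both arms. Any of these can move the secondary scores away from baseline without suction adding anything. If the abstract's sentence guided the report, improvement in the cupping arm could be presented as evidence of efficacy when sham patients had improved as much.

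For adverse events the wording fits worse still. Table 1 starts recording them at allocation, with no entry at screening, so there is no pre-treatment period of observation to compare with. Safety is a stated aim, and the Background names local blisters as the main expected reaction. Whether suction causes more of them can be learned only by comparing cupping with sham.

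**Working it through.** **1. Which comparison does each part of the article imply?**

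| Place | Outcomes covered | Comparison stated or implied |
|---|---|---|
| Abstract, Methods | All secondary outcomes, concomitant medication, adverse events | With baseline (stated) |
| Objectives and hypotheses | PASI | Cupping against placebo (stated) |
| Objectives and hypotheses | Secondary endpoints | None stated |
| Statistical analysis | PASI, DLQI, quality of life, VAS | Rank-sum test: independent groups (implied); Student t test: one-sample, paired or two-sample form not stated |
| Statistical analysis | Sex and age as the named qualitative variables | Chi-square or Fisher test: independent groups (implied) |
| Statistical analysis | Repeated quantitative measures | General linear model, contrast not stated |

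The within-patient counterparts would be the signed-rank test and McNemar's test. Neither is named. The analysis section therefore leans towards a between-arm comparison, but no sentence says so for the whole set of outcomes in the abstract.

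**2. The plan's own figure.** The Sample size section uses a formula for two independent proportions with p1 = 0.621, p2 = 0.353, two-sided α = 0.05 and power 0.80:

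n = [p1(1 − p1) + p2(1 − p2)] / (p2 − p1)² × (z0.975 + z0.80)²

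= 0.46375 / 0.071824 × 7.849 = 50.68, so 51 per group.

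Then 51 × 1.2 = 61.2, taken as 61, and 2 × 61 = 122. The stated size reproduces. It already rests on a two-arm comparison, so stating that comparison for the secondary outcomes does not alter it.

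**3. What would a literal test against baseline do if cupping added nothing?** Let both arms improve by the same amount d, in units of the SD of change. The article gives no SD for any secondary score, so d is an assumption. The one-sample t statistic for change in one arm has noncentrality d√n with n − 1 degrees of freedom. With n = 61 the two-sided 5% critical value is 2.00.

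| Assumed d | d√61 | Within-arm test significant, t test | Same, normal approximation | Between-arm test significant |
|---|---|---|---|---|
| 0.2 | 1.56 | 34% | 35% | 5% |
| 0.3 | 2.34 | 63% | 65% | 5% |
| 0.5 | 3.91 | 97% | 97% | 5% |
| 0.8 | 6.25 | about 100% | about 100% | 5% |

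With 51 per group the normal approximation gives 30%, 57%, 95% and above 99.9%. At d = 0 both tests reject 5% of the time, so the gap depends wholly on how much patients in both arms improve.

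**4. Adverse events.** No calculation applies. With recording from allocation onward, the baseline value is zero or undefined for events that arise on treatment, and any event at all counts as a rise from it. Only the difference between arms carries information about harm from suction.

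**The case against.** The strongest defence is that one clause in an abstract is not the analysis plan. It does not exclude a comparison with sham, and it names no test. The primary outcome uses similar language, "the proportion of patients with a reduction in PASI scores of ≥ 75% compared to baseline at the 4‑week follow-up visit", to define a measure for each patient, and its sample size rests on two groups. The abstract can be read the same way: change from baseline, then compared by arm. The analysis section names tests for independent groups and no paired test. Its lists in parentheses cannot be exhaustive, since the primary responder proportion is not listed among the qualitative variables either. Detailed assignment of variables to tests, and safety tables, are commonly left to a statistical analysis plan that is not shown here.

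Much of this stands. A reader might infer that the trial will test change from baseline in place of cupping against sham, or that it discards its randomised control. The documents do not support that: the named tests point the other way, and for DLQI and VAS a between-arm analysis is the likelier intent. Nor can one say that the trial will be unable to detect excess harm, because adverse events are collected in both arms. The omission of some variables from the analysis section is not, taken alone, an error.

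What remains is a comparator that is stated, that conflicts with the design, and that no other sentence corrects. Reading it as change from baseline, then compared by arm, makes sense for scores but not for adverse events.

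**Conclusion.** The point holds as a conflict of wording that needs reconciling. It is not proof of an analysis that ignores the control arm. The abstract states baseline as the comparator for the secondary outcomes and adverse events. The hypothesis, the design and the named tests imply cupping against sham. The analysis section does not settle the matter in words.

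If the abstract were followed literally, a secondary score on which both arms improved equally by 0.3 to 0.5 SD would be significant in about 63% to 97% of trials at 61 per group, instead of 5%. These percentages rest on assumed improvements, on approximately normal change scores and on all 61 patients being analysed. They show what the literal reading would cost, not what the trial will do. For adverse events the conclusion needs no such assumption. The weight is modest, but the correction is nearly free and removes a real ambiguity in how secondary efficacy and safety will be judged.

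**What to change.** - **Abstract:** replace the comparison with baseline by a comparison between cupping and sham for all the listed outcomes.
- **Statistical analysis, secondary outcomes:** state that body surface area, PGA, DLQI, quality of life, VAS and the TCM score are each compared between arms, adjusted for their baseline value, with a 95% CI. Use a method suited to the scale for ordinal scores such as PGA. Where a general linear model is used, name the between-arm contrast to be reported.
- **Statistical analysis, within-arm change:** state that it is descriptive only.
- **Statistical analysis, adverse events:** state that the proportion of patients with an event is compared between arms as a risk difference with a 95% CI.

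The cost is a few sentences. No data, visits or patients are added, and the planned 122 is unaffected. Baseline adjustment uses values already scheduled at allocation and, where baseline predicts outcome, gives a more precise estimate than the unadjusted t or rank-sum test. What is given up is the use of within-arm P values as evidence of benefit.

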**Discussion:**

The findings of this trial may lead to better decisions regarding the treatment of plaque psoriasis. If the trial outcomes are considered favorable, this ancient Chinese medical therapy may be worthy of widespread use because of its convenience and low cost.

**Trial registration:**

This study was registered on May 15,2019 at ClinicalTrials.gov with the identifier number NCT03952676.

## Background

Psoriasis is a chronic inflammatory skin disease that affects approximately 2–3% of the global population [1, 2]. It is characterized by epidermal hyperproliferation, abnormal keratinocyte differentiation, angiogenesis with blood vessel dilatation, and excess T-helper cell type 1 (Th1) and Th17 inflammation [3]. The plaque type is the most common form of psoriasis, accounting for 85–90% of psoriasis cases [1]; it leads to detrimental physical effects and reduced psychological well-being [4, 5]. It is also closely related to metabolic syndrome, cardiovascular disease, and chronic obstructive pulmonary disease [6]. For most patients, psoriasis results in the restriction of various aspects of everyday life, enormous personal costs, and mental stress [7].

The current treatment for psoriasis primarily comprises local and systemic treatments. Local treatment mainly comprises hormonal drugs and calcineurin inhibitors, and systemic treatment comprises etretin, immunosuppressants, and biological agents [8]. However, the various side effects and high economic costs limit the clinical application of these treatments [7]. Therefore, developing or identifying safe and effective treatments for psoriasis has major social and economic benefits.

Recently, complementary and alternative medicine (CAM) therapies have become an increasingly important area of dermatology, and cupping is becoming an important CAM therapy. Cupping is an ancient method that has been used worldwide. From ancient Egypt to the Han Dynasty in China [9, 10], and from Hippocrates in Greece to the early Islamic period [11, 12], there have been numerous descriptions of cupping treatments for various diseases. Cupping is currently used to treat a wide range of medical conditions [13, 14], and randomized controlled trials (RCTs) have confirmed the efficacy of cupping for certain pain-related diseases such as osteoarthritis of the knee and chronic low back pain [15, 16]. There are two types of cupping methods; dry and wet. Moving cupping therapy is a unique dry method that has been used as a traditional treatment for thousands of years. This method involves the application of lubricant to the body part or to the mouth of the cup and using the flashing method or the cotton sticking method to adsorb the cup to the treatment area. The cotton sticking method involves pasting cotton soaked in alcohol on the inner wall of the cup; it is then ignited and adsorbed on the treatment area, but the skin may be scalded due to the excessive dripping of alcohol. The flashing method quickly withdraws the cotton soaked in alcohol. This is a safe and common method of cupping. The physician pushes the cup by hand to move it up and down and left and right, thus causing flushing, congestion, and even ecchymosis of the skin in the treatment area [17]. Therefore, moving cupping therapy integrates the functions of warm moxibustion (which involves lighting the moxa stick and hanging it at a certain distance from the skin), cupping, scraping, massage, and drug therapy, and it has a wide range of clinical applications. This therapy has the ability to regulate immune function [18, 19], thereby improving skin tolerance [20, 21]. Psoriasis damages the epidermis, which destroys the human skin barrier composed of keratinocytes, intercellular substance, natural moisturizing factors, and sebum membranes. The Koebner phenomenon illustrates the important relationship between an impaired skin barrier and psoriasis [22, 23]. Moving cupping treatment can cause the mechanical stimulation of pulling and is beneficial for the secretion of sebaceous glands and sweat glands, and the use of lubricants can significantly improve the skin barrier function. Psoriasis is also known to be closely related to lipid metabolism [24]. Cupping therapy can upregulate anti-inflammatory lipids, downregulate the function of pro-inflammatory lipids, improve the balance of lipid metabolites, and alleviate the inflammatory response [25].

Moving cupping therapy has been widely used for the treatment of plaque psoriasis, which is safe and associated with few adverse reactions, mainly local blisters. Additionally, it has been recognized by a large number of peers and patients. One study compared the efficacy of moving cupping and narrowband ultraviolet B based on oral Chinese herbs and found that moving cupping has clear advantages, but lacked high-quality medical evidence [26]. Therefore, we designed a multicenter, prospective, single-blind, placebo-controlled, RCT to evaluate the safety and efficacy of moving cupping therapy for plaque psoriasis.

### Objectives and hypotheses

Moving cupping is widely used as a CAM therapy. The aim of this RCT is to evaluate the efficacy of moving cupping as a plaque psoriasis treatment. The hypothesis of this study is that the Psoriasis Area and Severity Index (PASI), used as the primary endpoint to demonstrate the clinical efficacy of plaque psoriasis treatment, will be decreased significantly with moving cupping treatment compared to placebo treatment [27]. Secondary endpoints, including body surface area (BSA), Physician’s Global Assessment (PGA), Traditional Chinese Medicine syndrome scoring scale (TCMSSS), and patient-reported outcomes (Dermatology Life Quality Index [DLQI] and visual analogy scale [VAS]), for the evaluation of post-treatment clinical efficacy, psychology, quality of life, and degree of pruritus will also be considered. This study complies with the relevant Standard Protocol Items: Recommendations for Interventional Trials (SPIRIT) Checklist (Supplementary file 1) [28].

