### Sample size

The sample size of the current trial was calculated based on the following formula [33]:
$$ {\mathrm{n}}_1={\mathrm{n}}_2=\frac{p_1\times \left(1-{p}_1\right)+{p}_2\times \left(1-{p}_2\right)}{{\left({p}_2-{p}_1\right)}^2}\times {\left({\mu}_{\alpha /2}+{\mu}_{\beta}\right)}^2 $$

According to recently published clinical trial results [27], the PASI-50 reached 62.1% (P_1_) in the study group and 35.3% in the control group (P_2_). Therefore, we assumed that the inspection level (α) was 0.05 and the power was 0.8 (β = 1-power = 0.2). For the two-sided tests, 51 participants will be required for each group. Given a 20% loss to follow-up, we expect to require 61 participants for each group. Therefore, this trial will require at least 122 participants.

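### The primary endpoint is stated inconsistently: a falling PASI score in the hypothesis, a PASI-75 proportion in the outcome definition, and no test tied to PASI-75 in the analysis section

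*Protocol article*

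**What the plan says.** Five places in the protocol article bear on this point.

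- **Objectives and hypotheses.** PASI is "used as the primary endpoint to demonstrate the clinical efficacy of plaque psoriasis treatment, will be decreased significantly with moving cupping treatment compared to placebo". No responder threshold or time point is given.
- **Primary parameters.** "The primary outcome of the RCT is the proportion of patients with a reduction in PASI scores of ≥ 75% compared to baseline", assessed at the 4-week visit. This is a binary outcome.
- **Statistical analysis.** PASI is grouped with the continuous measures: "quantitative variables (PASI, DLQI, R-QoL, VAS) with normal distributions will be described as means and standard deviation". "Quantitative variables will be compared using a Student" t test, or by a Wilcoxon rank-sum test if not normal, and "Quantitative variables with repeated measures will be applied with general linear models". The only examples of categorical data are in "Qualitative variables (sex, age) will be summarized as frequency and proportions", for which chi-square or Fisher tests are offered. PASI-75 is not mentioned, and no test is called primary. The threshold is P < 0.05.
- **Sample size.** A two-proportion formula is applied to PASI-50 rates of 62.1% and 35.3%: "we assumed that the inspection level (α) was 0.05 and the power was 0.8". This gives 51 per group, raised to 61 for loss to follow-up.
- **Missing data.** Dropouts are counted as non-success.

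**The concern.** A lower mean PASI and a higher proportion passing a 75% reduction are different variables, with different estimands and tests, and they can disagree on the same data. The hypothesis and the placement of PASI in the analysis section point to the score. The formal outcome definition points to the proportion.

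The practical risk is a score comparison that succeeds while the PASI-75 comparison does not. The hypothesis section would then let the result be described as meeting the primary endpoint. The sample size adds a third version, PASI-50, so the stated power belongs to neither of the two.

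**Working it through.** **1. The plan's own figure.** Inputs from Sample size: p1 = 0.621, p2 = 0.353, two-sided α = 0.05, power 0.80.

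n = [p1(1−p1) + p2(1−p2)] / (p1−p2)² × (1.960 + 0.842)²
= (0.2354 + 0.2284) / 0.0718 × 7.849 = 50.7, so 51 per group.

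51 × 1.2 = 61.2, taken as 61 per group, 122 in total. The figures reproduce, but only for PASI-50.

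**2. Which endpoint the sections imply.**

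| Section | Form of PASI implied |
|---|---|
| Objectives and hypotheses | Score that decreases |
| Primary parameters | PASI-75 proportion, 4-week visit |
| Statistical analysis | Quantitative variable; PASI-75 not named |
| Sample size | Proportion, but PASI-50 |
| Missing data | Binary (non-success) |

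Three sections fit a proportion and two fit a score. None links PASI-75 to a test.

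**3. False-positive rate if either test may be claimed.** Assumptions: 61 per arm with no dropout; percent PASI reduction normal, capped at 100; SD 20, 30 or 40 points. The documents give no SD. A t test on percent reduction and a two-proportion test on reduction ≥ 75% were run on the same data with no true effect (40,000 trials per setting, several mean levels). Each test alone rejected in about 5% of trials. At least one rejected in 7.8% to 9.0%. This is given as about 7–9% to allow for other mean levels. Two independent tests would give 1 − 0.95² = 9.75%.

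**4. Power for each form, calibrated to the plan's PASI-50 rates.** On the normal scale the arms lie 0.308 − (−0.377) = 0.685 SD apart. The chosen SD then fixes the PASI-75 rates.

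| SD (points) | PASI-75 rates | PASI-75 power, 51 per arm | PASI-75 power, 61 per arm | Tests disagree, 61 per arm |
|---|---|---|---|---|
| 20 | 17.3% vs 5.2% | 50% | 58% | 39% |
| 30 | 30.0% vs 11.3% | 66% | 74% | 23% |
| 40 | 37.6% vs 15.8% | 72% | 79% | 18% |

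The score comparison has about 92–93% power with 51 per arm and 96% with 61. Nearly all disagreements are trials in which only the score is significant (38%, 23% and 17% of all trials at SD 20, 30 and 40).

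For 80% power, PASI-75 needs about 106 (SD 20) to 64 (SD 40) per arm before dropout by the pooled two-proportion formula. The same formula gives 54 for the plan's PASI-50 rates.

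**5. Dropouts as non-responders.** With 20% loss in both arms, the PASI-50 rates become 0.621 × 0.8 = 0.497 and 0.353 × 0.8 = 0.282. Power with 61 per arm is then about 68%. Step 4 does not include this loss, so PASI-75 power under that rule would also be lower than shown.

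**The case against.** The best defence is that the hypothesis only names an instrument and a direction, and that Primary parameters then makes it operational. That section is the only formal definition and gives measure, threshold and visit. The two-proportion formula and the non-success rule both suit a binary outcome. This stands, and it makes a responder proportion the likelier intent.

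A reader might infer that the analysis section, followed literally, yields only a score comparison. The text does not support that. Chi-square and Fisher tests are offered for qualitative variables, and a responder proportion is one. The bracketed lists are not exhaustive, since PGA, BSA and TCMSSS appear in neither. Weekly PASI scores would also need a quantitative summary under any primary endpoint.

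A reader might also infer that the plan inflates the type I error to 8–9%. No section permits choosing the test after seeing the results. The figure is what would follow if that choice were made, not a property of the plan as intended.

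An unseen analysis plan may name the primary test. That would settle the analysis, but it would not make these sections of the article agree.

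**Conclusion.** The inconsistency is real and does not depend on any calculation. It is a conflict of wording about what counts as trial success, with one reading clearly likelier, and not a plan with two declared primary tests.

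If left open, its size is about a 7–9% false-positive rate in place of 5%, conditional on either test being claimable. With 61 per arm, the two forms would disagree in roughly 18–39% of trials at the plan's own PASI-50 effect. Settling on PASI-75 means the stated 80% power no longer applies: about 58–80% with 61 per arm and 50–72% with 51. All these figures rest on an assumed normal percent reduction with SD 20–40 points, because the documents give neither an SD nor PASI-75 rates.

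**What to change.** - **Objectives and hypotheses:** restate the hypothesis as a higher proportion with at least 75% PASI reduction at week 4 on moving cupping than on placebo.
- **Statistical analysis:** name PASI-75 at week 4 as the single primary variable, compared by chi-square or Fisher test with dropouts as non-responders. List PASI score or percent change as secondary, with no claim of primary success from it.
- **Sample size:** do not carry the PASI-50 power over. Restate power for the endpoint kept, with PASI-75 rates given and justified and the non-responder rule applied.

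The first two changes are wording and should be made before unblinding. There are two costs. The sponsor gives up the more sensitive score comparison as primary. The stated power also becomes less favourable, and the restated calculation may call for more patients.
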